## Abstract

Cumulative experiences of racism lead to stress and trauma. Racial trauma is associated with compromised functioning across psychological, social, and physical health domains. This is further complicated by any comorbidity with other mental health conditions. Many clinicians are not trained in identifying, diagnosing, and treating racial trauma. Given the pervasive nature of racism, limited clinician knowledge and experiences, as well as the impact of this condition, there is an urgent need for novel, culturally safe, and effective treatment. The newly developed Healing Racial Trauma Protocol (HRTP) shows significant promise. We explore the methodological considerations for a randomized controlled trial comparing the efficacy of the HRTP for racialized individuals suffering from racial trauma and to a control condition of treatment as usual, in reducing the severity of racial trauma and depression symptoms, as well as improved functioning. Ethical, pragmatic, and methodological considerations in trial design, research population, and treatment protocol are explored.

## 1. Introduction

People of colour experience a range of health disparities rooted in the consequences of racism (Cénat et al., 2023; Williams et al., 2022b). These health disparities are further exacerbated by challenges in access to timely, quality, and culturally safe healthcare services, including prevention and treatment. *Racial trauma* refers to the traumatic effects of individual and systemic racism over time, which can often match the severity and symptomatology of posttraumatic stress disorder (PTSD; Cénat, 2023; Williams & Zare, 2022). The early detection, diagnosis, and treatment of racial trauma is critical to mitigate the deleterious effects of racism on quality of life, chronic health risks, and social relationships. Evidence for the efficacy of conventional PTSD treatment to address trauma in people of colour is limited due to the lack of ethnoracial representation in research, poor reporting standards for race-based data, and the limited ethnoracial diversity of clinicians (Faber et al., 2023b). Therefore, evidence of novel, culturally safe, and effective treatment approaches is essential. Specifically, a targeted clinical trial can provide empirical evidence for the efficacy of a culturally safe racial trauma-specific treatment compared to a conventional treatment approach. This paper outlines the methodological considerations of the trial design, research population, and treatment protocols for a randomized controlled trial for the treatment of racial stress and trauma for Canadians of colour.

### 1.1. Mental Health Disparities Among Racialized Communities

There has been a steady increase in Canada’s racialized population due to increasing population growth and immigration. The population of racialized Canadians increased by 130% from 2001 to 2021 compared to a 1% increase among White Canadians (Statistics Canada, 2023). Two thirds of this growth are attributed to the arrival of new immigrants, while one third is attributed to a Canadian-born population (Statistics Canada, 2023). In 2021, 5% of the population in Canada was Indigenous, and one in four Canadians (26.5%) were racialized, reaching a population of 9 million. From the racialized groups, South Asian people represented 26%, Chinese people 18%, and Black people 16% (Statistics Canada, 2023). Racialized communities reflect diverse cultures, social identities, and experiences. Race and ethnicity often intersect with other social identities based on gender, sexuality, disability, language, socioeconomic circumstances, and education. For many racialized groups, the process of racism leads to their differential treatment due to people’s perception of their shared appearance and presumed ancestry (Holmes et al., 2024). Racism impacts mental health disparities through access to opportunities (e.g., employment, housing, education), exposure to risk factors (e.g., environmental risk, violence), patterns in cognitive and emotional processes associated with psychopathology, and behaviours related to coping and self-regulation (Lewis et al., 2015; Paradies et al., 2015).

Many racialized Canadians experience health disparities in both physical and mental health conditions rooted in racism and systemic oppression, which is further exacerbated by limited access to timely and quality healthcare (Faber et al., 2023b; Lewis et al., 2015). Racialized communities face increased risk and diagnosis of specific mental health conditions, while also being underdiagnosed for other conditions (Cénat et al., 2024; Public Health Agency of Canada, 2024; Faber et al., 2023a). These experiences are further exacerbated by additional barriers, including financial constraints, fear of discrimination from service providers, and a lack of representation among mental health professionals (Faber et al., 2023b). Further, inequities in conditions and access are more pronounced for people with intersecting identities (Williams et al., 2023b).

Lastly, the lack of race-based data in Canada makes it harder to address these disparities, leaving racialized individuals without adequate support. Only recently has Canada prioritized the collection and analysis of race-based data to examine disparities in life conditions, health inequities, and access to care (Sheikh et al., 2023; Williams et al., 2024b). However, many health and social services institutions do not routinely collect data on race and ethnicity to examine disparities in health conditions and access. This is further hindered by the lack of data on intersecting identities, such as immigration status, language minorities, region, gender, and disability, among others. The collection and analysis of disaggregated sociodemographic data is essential to assess and address disparities at a granular level and make more informed decisions.

#### Racial Stress and Trauma

Among the mental health inequities faced by Indigenous peoples and racialized communities, racial trauma is a condition associated with negative impacts across psychological, social, and physical health domains (Cénat, 2023; Williams & Zare, 2022). Despite Canada’s commitments to multiculturalism and inclusion, systemic racism and discrimination create significant stress. Racial trauma results from direct or repeated experiences of racism, including microaggressions, exclusion, and institutional discrimination. This condition can also co-occur with other mental health challenges, including anxiety, suicidal ideation, depression, despair, and poor physical health (Bellamy & Hardy, 2015; Williams & Zare, 2022), which can go undiagnosed and often unrecognized by mainstream mental health providers. Although many therapists report serving clients with symptoms of racial trauma, few have sufficient training in the assessment and treatment of this condition (Hemmings & Evans, 2018).

Several theoretical frameworks have identified the pathways linking racism to poor mental health in general. However, few models have examined the link between racism and racial trauma. Williams and colleagues proposed a framework to understand the mechanisms that link the cumulative effects of racism with racial trauma, which often manifests through symptoms of PTSD (Williams et al., 2018a, 2022c, 2023a). This model identified risk factors associated with historical and cultural trauma and race-based oppression, as vulnerabilities that interact with cumulative life experiences related to covert and overt racism. For a racialized person, racially charged traumatic events can result in intense emotional responses of shock, fear, and anger. When these experiences are invalidated, across time and people, PTSD-like symptoms can develop including intrusive thoughts, avoidance, negative changes in mood and cognitions, as well as changes in physical and emotional arousal. With time, these experiences are exacerbated by limited access and barriers to quality and timely care due to institutional racism. That is, a care provider might have limited knowledge of or a reluctance to address issues of race and racism in the therapeutic setting.

Based on this framework and the existing literature, researchers have identified key components essential to treating racial trauma (Carlson et al., 2018; Chavez-Dueñas et al., 2019; Comas-Díaz, 2016; Reynolds, 2019; Bartlett et al., 2022), yet, there still is no adapted CBT treatment specific for racial trauma with evidence of efficacy through a randomized clinical trial.

### 1.2. A Promising New Intervention: The Healing Racial Trauma Protocol

Although racial stress and trauma are common, there are few evidence-based manualized treatments available for people of colour suffering from racial trauma (Williams et al., 2021). *The Healing Racial Trauma Protocol* (HRTP) is an innovative treatment protocol that provides a detailed approach on how to help people suffering from racial stress and trauma through guided content over 12 sessions (Williams, 2024). This therapy comprises a total of 12 sessions (each session is 1 h), delivered weekly over a period of 3 months. Grounded in cognitive behavioural therapy (CBT), as well as the third-wave behavioural approaches of Functional Analytic Psychotherapy (FAP) and Acceptance and Commitment Therapy (ACT), this protocol has three sections. The first section is Stabilization and Support, which consists of the first three sessions. The second is Healing the Wounds of Racism, which includes the next 4–5 sessions, and the third section is Empowerment, which includes the last 4 sessions. The structure of these sections is similar to Herman’s three stages of psychological trauma recovery (2015), which include establishing safety, retelling the story of the traumatic event, reconnecting with others, and empowerment.

The HRTP is culturally safe primarily because it recognizes that the most significant source of therapeutic safety is not the protocol itself, but rather the clinician who delivers it. Although the techniques used in the HRTP have been vetted through research studies and reflect widely accepted therapeutic approaches (e.g., CBT, FAP, and ACT; Holmes et al., 2024; Williams et al., 2023a), these methods alone cannot ensure cultural safety. Instead, the clinician’s capacity to create a safe and validating environment—through ongoing education, cultural competency training, and personal anti-bias work—is what ultimately fosters a secure therapeutic space (Williams et al., 2022a). This emphasis on the clinician’s role acknowledges the importance of addressing power dynamics, historical injustices, and the lived experiences of racialized clients in the therapeutic process.

In practice, the HRTP demands that clinicians be mindful of how systemic and individual biases can emerge, even within well-intentioned therapeutic contexts. By requiring that clinicians reflect on their own biases, develop cultural humility, and engage in continuous learning, this ensures an appropriate base level of safety for participants. It exemplifies an approach in which therapeutic exercises are informed by evidence-based principles and also tailored to honour and validate each client’s cultural identity and lived reality. In this way, the HRTP situates itself within a framework of cultural safety that moves beyond specific CBT techniques, centering relational factors that are critical to the healing process.

### 1.3. Need for More Inclusive Clinical Research

Clinical trials are widely regarded as the gold standard for establishing evidence-based clinical treatment options. They play a critical role in evaluating the efficacy of new therapies, like the HRTP, as well as providing specific methodological frameworks to guide practice. Novel treatment options, in particular, depend on rigorous clinical trial data to demonstrate their safety and effectiveness. However, to date, racialized populations have been disproportionately excluded from such trials, skewing the evidence base and limiting the generalizability of findings (e.g., Polo et al., 2019; U.S. Food & Drug Administration, 2021). This is a pressing concern, as many racialized groups—including Black and Indigenous populations—experience disproportionately high rates of trauma (Grau et al., 2022). Yet they remain underrepresented in PTSD and other mental health research (Grau et al., 2022; Reid & Buchanan, 2024). Consequently, entire approaches intended to alleviate suffering and address mental health concerns have historically omitted large segments of racialized communities (Misra et al., 2023).

Several factors contribute to the exclusion of racialized groups from clinical trials, all of which are rooted in systemic and structural racism. First, many racialized people harbour deep mistrust of the medical and research establishment, a sentiment driven by well-documented historical abuses and continued experiences of medical racism (e.g., Miola et al., 2025; Stewart & Gonzalez, 2023). Second, researchers frequently operate under biassed assumptions that racialized individuals will not be reliable participants, leading to higher exclusion rates (e.g., Passmore et al., 2021). Finally, the lack of culturally informed methodologies hinders effective recruitment and retention of diverse groups, ultimately reinforcing existing disparities in mental health research (e.g., Waheed et al., 2015; M. Williams et al., 2013; M. T. Williams et al., 2013). Addressing these systemic barriers is essential for developing inclusive, equitable, and culturally informed approaches to treating racial trauma.

### 1.4. The Goals of the Current Study

The primary objective of this paper is to describe a randomized controlled trial that will compare the efficacy of the HRTP for people of colour suffering from racial trauma compared to a control condition of treatment-as-usual (TAU) in reducing the severity of racial trauma and related symptoms, as well as improving functioning. This paper will provide preliminary feasibility evidence in terms of implementation, practicality, and acceptability for clients and therapists. Additionally, we will outline methodological approaches to trial design, the research population, and treatment protocols. That is, methodological approaches which could serve as inclusive and viable models for engaging in clinical research related to racialized populations. Specifically, the proposed trial will examine: (a) whether the administration of the HRTP will result in a clinically significant reduction in racial trauma symptoms in participants compared to the TAU control group, and (b) whether any clinically significant reduction in racial trauma symptoms is maintained long-term (i.e., 4 months after the intervention).

It is hypothesized that the completion of the 12-session HRTP will result in a clinically significant improvement in participants’ racial trauma symptoms and severity, as well as improved functioning. It is also hypothesized that these changes will be greater than changes in the control conditions and will be maintained 4 months following the completion of the intervention.

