### 2.2. Sample Size, Randomization, and Allocation

A sample of 96 participants (48 per group) is needed for an 80% probability to identify a difference between the treatment and control group. The power analysis for the sample size estimation was based on the means, standard deviations, and clinical cut-off for the primary outcomes (RTS, TSDS; Williams et al., 2022c, 2023b). Drawing on previous research, we hypothesized a standard mean difference of between 0.36 and 0.52, between the treatment and control group, which translates to a 10–20% decrease in the primary outcomes (i.e., RTS, TSDS) for individuals at the endpoint of treatment. Given these effect estimates, with an alpha of 0.05, an 80% power, and a 20% attrition, we estimated a sample size of approximately 96 (48 per group) will be needed. This randomized controlled trial will use an ANOVA and t-test (alpha error level = 5%, two-sided) for independent samples.

This sample size will require tailored recruitment efforts, community partnerships, and culturally safe retention strategies throughout the trial. Given differential attrition rates for racialized communities, the research team will spend additional time at intake discussing barriers to participation, issues with attendance, and address any participant concerns. Additionally, the research team will offer flexible session meeting times (e.g., evenings and weekends), and telephone check-ins as needed. The research team shall also compensate participants for both their completed sessions and batteries of measures.

In terms of blinding, the trial research team will be unaware of the group allocation. This includes the principal investigator and project coordinator who are overseeing the trial implementation, research assistants who will support recruitment and data collection, and the statistician conducting the analysis. See Figure 1 for the participant flow diagram of the trial.

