### 2.12. Statistical Analysis

Descriptive statistics, including means, standard deviations, and frequencies, will be calculated for continuous primary and secondary outcomes. Differences in primary and secondary outcomes, including TSDS, RTS, change in symptoms, and therapeutic experiences, will be examined using a two-way mixed ANOVA with two or three within-subject levels of time (pre-test, post-test, and follow-up) and two between-subject levels of condition (HRTP and control). When there is evidence of sphericity violation, we will use the Greenhouse–Geisser correction (Greenhouse & Geisser, 1959). It is predicted that participants’ TSDS and RTS scores will decrease significantly over the course of the treatment. It is also predicted that TSDS and RTS scores at follow-up will be the same or lower than at the end of the treatment.

Both the short-term and long-term efficacy of the HRTP will be examined during the treatment (week 0, 4, 8), at the end of the treatment (week 12), and 4 months after the treatment (week 28). Assessment will take place at four time points for the treatment group (HRTP therapy; weeks 0, 4, 8, 12, and 28; see Table 1 for participants’ assessment schedule) and only two time points for the control TAU group (T0 and T4; see Table 1 for participants’ assessment schedule). Analysis will compare standard mean differences (SMDs) between the time points for the treatment group (weeks 0, 12, and 28) and the control group (weeks 0 and 12). Analyses will entail intent to treat (ITT) and include participants with pre-treatment and the last time point available as long as they attended at least one treatment session. We examine significant levels for the analysis as well as effect sizes. A significance level of *p* < 0.05 will be used for all tests.

For each outcome of interest, we will identify any significant Condition × Time interactions. When no interaction is found, significant main effects will be reported. Partial eta-squared (η2) was used to measure effect sizes for the ANOVAs. When significant interactions are found, post hoc tests of simple main effects will be used to examine the differences, *p* values will be included for all post hoc tests, and 95% confidence intervals (CIs) will be used for all *p* values less than 0.05. Additionally, we will conduct comparisons of baseline data for completers and non-completers. Subgroup analysis will be based on age, gender, and levels of racial stress and trauma.

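### The aims and hypothesis concern clinically significant change in racial trauma, but the stated analysis has no criterion for it and does not use the clinical cut-off cited in planning

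*Protocol article*

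**What the plan says.** Section 1.4 of the protocol article uses the clinical term three times. Aim (a) is that HRTP "will result in a clinically significant reduction in racial trauma symptoms in participants compared to the TAU control group". Aim (b) is "whether any clinically significant reduction in racial trauma symptoms is maintained long-term (i.e., 4 months after the intervention"). The hypothesis is that the twelve sessions "will result in a clinically significant improvement in participants’ racial trauma symptoms and severity, as well as improved functioning".

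Section 2.12 sets out the analysis. Outcomes "will be examined using a two-way mixed ANOVA with two or three within-subject levels of time (pre-test, post-test, and follow-up") and two levels of condition. It adds: "Analysis will compare standard mean differences (SMDs) between the time points for the treatment group (weeks 0, 12, and 28"), with weeks 0 and 12 for the control arm. It continues: "We examine significant levels for the analysis as well as effect sizes". The decision rule is "A significance level of *p* < 0.05 will be used for all tests". Partial eta-squared is the ANOVA effect size, and 95% confidence intervals are tied to p values below 0.05. The predictions in this section are about scores: a significant fall during treatment, and no rise by follow-up.

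Section 2.2 says that the power analysis was "based on the means, standard deviations, and clinical cut-off for the primary outcomes", namely the RTS and TSDS. It gives no value for the cut-off, and section 2.12 does not mention it.

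**The concern.** The aims ask whether a change is large enough to matter clinically. The analysis asks whether mean scores differ, and by how many standard deviations. Nothing in the article joins the two: there is no minimal important difference, cut-off analysis, reliable-change rule or responder definition.

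Two conclusions are at stake. For aim (a), a significant condition-by-time interaction would be the natural basis for claiming success, with no pre-specified standard for the word clinical. For aim (b), maintenance of a clinically significant reduction cannot be judged until it is settled who achieved one. Because intervals accompany only significant results, a non-significant result could not be read against a clinical threshold either.

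**Working it through.** **1. Aims and analysis side by side.**

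| Item | Section 1.4 | Section 2.12 |
|---|---|---|
| Aim (a), week 12 | Clinically significant reduction versus TAU | Difference in mean scores, p < 0.05, SMD, partial eta-squared |
| Aim (b), week 28 | Clinically significant reduction maintained | Mean score the same or lower than at end of treatment |
| Threshold | Implied by the term | None |

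**2. Does another part of the article supply the criterion?**
- Section 2.2 names a clinical cut-off, as a sample-size input only. The 10–20% decrease given there is the hypothesised effect and is not called a clinical threshold.
- UnRESTS, the interview that defines clinically relevant racial trauma at entry (sections 2.3 and 2.8), is scheduled at week 0 only (Table 1). Loss of diagnosis therefore cannot be the criterion.
- RTS and TSDS are collected in both arms at weeks 0 and 12, and in the HRTP arm at week 28 (section 2.9, Table 1). They are the scheduled racial-trauma measures that could carry a criterion.

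**3. What p < 0.05 shows at this sample size.** The plan states no figure for clinical significance, so there is none to reproduce. Inputs: 48 per arm and 20% attrition (section 2.2), so 48 × 0.8 = 38.4, taken as 38 completers per arm. For a two-sided independent-samples t-test, the smallest observed SMD that is significant is

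d_min = t(0.975; 2n − 2) × √(2/n)

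- n = 48: 1.986 × 0.2041 = 0.41
- n = 38: 1.993 × 0.2294 = 0.46

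With the same standard error, the 95% interval is d_min ± d_min: about 0 to 0.81 with 48 per arm, and about 0 to 0.91 with 38. A result that just reaches significance is thus compatible with almost no benefit. The ANOVA interaction would give a different d_min, depending on a pre–post correlation that the article does not state, but at p = 0.05 the interval for that contrast also starts at zero.

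**4. What a responder comparison could deliver.** The documents give no responder rate, so these are assumptions: control rate p_C of 20–50%, a normal model, and the planned SMD of 0.36 to 0.52 (section 2.2) as the shift.

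p_H = Φ(Φ⁻¹(p_C) + SMD)

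Power = Φ{[(p_H − p_C) − 1.96·√(2p̄(1 − p̄)/n)] / √([p_C(1 − p_C) + p_H(1 − p_H)]/n)}, where p̄ is the mean of the two rates.

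| p_C | SMD | p_H | Power, n = 48 | Power, n = 38 |
|---|---|---|---|---|
| 0.20 | 0.36 | 0.315 | 25% | 21% |
| 0.20 | 0.52 | 0.374 | 47% | 39% |
| 0.30 | 0.36 | 0.435 | 28% | 23% |
| 0.30 | 0.52 | 0.498 | 51% | 42% |
| 0.40 | 0.36 | 0.542 | 29% | 24% |
| 0.40 | 0.52 | 0.605 | 52% | 43% |
| 0.50 | 0.36 | 0.641 | 28% | 23% |
| 0.50 | 0.52 | 0.698 | 51% | 42% |

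Across these settings power runs from about 21% to 52%.

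**The case against.** The best defence is that this is only a missing definition. A journal article condenses, a responder rule often sits in the full protocol or SAP, and section 2.2 suggests that a cut-off exists. The analysis also plans effect sizes and some confidence intervals, and section 2.12 never calls a p value clinical significance.

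Part of this stands. The plan is not p values alone, a definition may exist elsewhere, and mislabelling of results is a risk, not something the text commits. But the article states its aims and its analysis in some detail, and the two do not match. Effect sizes without a benchmark do not settle whether a change is clinically significant.

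Three stronger readings are tempting but not supported:
- *The trial cannot answer its question.* The RTS and TSDS data needed for aim (a) are collected in both arms. The gap is in the analysis.
- *Aim (b) has no outcome.* Both scales are measured at week 28 in the HRTP arm. What is missing is a criterion, and a control measurement at that time.
- *The planned SMD is smaller than a reliable individual change and so clinically trivial.* A reliable-change threshold concerns measurement error in one person's score, which averages out in a group mean. It cannot be set against a between-arm SMD. The RTS reliability of 0.97 is also an internal-consistency alpha, not a test–retest value. The BDI-II has no place in such a comparison: these aims concern racial trauma, and the planned SMD is stated for RTS and TSDS only.

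**Conclusion.** The concern holds in this form: the aims and hypothesis are phrased as clinically significant change, and the stated analysis neither defines nor tests it, although a clinical cut-off is said to have informed planning. This rests on the text and needs no assumption. The figures of 0.41 and 0.46 illustrate why significance is no substitute. They assume a two-arm t-test at week 12 with 48 or 38 per arm. The 21–52% power range rests on assumed responder rates and affects only how the remedy should be used. The article should be corrected on this point, but the mean-score comparison can stay as the main analysis.

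**What to change.** In section 2.12:
1. Define a clinically significant change on the RTS in advance: reliable improvement, 1.96 × SD × √(2(1 − r)) with the source of SD and r stated, together with a week-12 score below the cut-off named in section 2.2, whose value should be given.
2. State how participants already below that cut-off at baseline are counted (entry is by UnRESTS, so there may be some), and how randomised participants with missing data are counted.
3. Report the proportion per arm at week 12 with a risk difference and 95% CI, as a secondary analysis aimed at estimation.
4. Report the 95% CI of the mean difference whatever its p value.
5. Do the same for the TSDS once its reliability and cut-off are stated; section 2.9 gives no TSDS reliability.
6. Describe week 28 within the HRTP arm only, since TAU has no measurement then.

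The alternative is to remove the term clinically significant from the aims and hypothesis in section 1.4, and state them as differences in mean score.

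The cost is one additional analysis of data already scheduled. The drawback is the low power of the binary comparison, so a non-significant risk difference must not be read as absence of clinical benefit.
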